### Trial design {8}

The study is designed as a prospective, cluster-randomized, multicenter interventional pilot trial. It employs a cluster-randomized design, where each participating EMS region in pre-defined time frames represents a cluster. The clusters will be randomly allocated to either the intervention group (receiving a PEEP of 5 mbar) or the control group (receiving ZEEP or 0 mbar) for a defined period of 6 months, followed by a crossover, where the same regions will switch to the opposite treatment arm for another 6 months.

The allocation ratio is 1:1 within each cluster, meaning that each group (intervention and control) will receive an equal number of patients. Since this is a pilot study, it is designed primarily to assess the feasibility and preliminary effects of the intervention rather than to definitively establish superiority. The results will provide the groundwork for future, more extensive studies.

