## Assignment of interventions: allocation

### Sequence generation {16a}

In this study, the allocation sequence will be generated using *cluster randomization*. Each participating EMS region (Gütersloh, Minden-Luebbecke, and Osnabrueck) will represent a cluster. The clusters will be randomized to either the intervention group (PEEP) or the control group (ZEEP) using *predefined randomization blocks*, which are based on 6-month intervals. After 6 months, the clusters will switch to the opposite group, ensuring that each region experiences both interventions.

To reduce predictability and maintain the integrity of the randomization, the allocation sequence and any randomization restrictions, such as block sizes, will be managed centrally and will not be accessible to the EMS personnel enrolling participants or assigning interventions. This ensures that the allocation remains concealed until implementation.

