## Statistical methods

### Statistical methods for primary and secondary outcomes {20a}

For the primary outcome (ROSC), a mixed logistic regression model will be used to analyze the difference in the probability of achieving ROSC between the two groups (PEEP vs. ZEEP). This model will account for the cluster-randomized design, adjusting for potential correlations within clusters (EMS regions).

For secondary outcomes, such as re-arrest rate, death during pre-hospital care, hospital admission during ongoing resuscitation, hospital admission with spontaneous circulation, SpO₂, FiO₂, and etCO₂ at hospital admission, linear regression models will be used for continuous variables, while logistic regression will be applied for binary outcomes (e.g., shockable vs. non-shockable rhythms).

The models will include relevant covariates, such as age, comorbidities, and other baseline characteristics, to adjust for potential confounders. Random effects will be included to account for variability between EMS regions.

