### Additional statistical considerations

All analyses will be conducted on an intention-to-treat basis. Exploratory subgroup analyses are planned to evaluate potential effect modifications, including presumed etiology of OHCA (respiratory/asphyxial vs. primary cardiac) and airway management difficulty. These analyses will be hypothesis-generating and interpreted with caution.

The study hypothesis is that ventilation with PEEP (5 mbar) increases the probability of ROSC compared with ZEEP (0 mbar).

No interim analyses are planned.

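### The primary model clusters by region only, with no period effect or region-period component, so the ROSC interval is too narrow whenever ROSC varies between periods within a region

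*Protocol article*

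**What the plan says.** Trial design {8} states that "each participating EMS region in pre-defined time frames represents a cluster". Three regions and two 6-month time frames give six such units. The same section says allocation is 1:1 within each cluster. That fits a region followed over both periods, but not a region-period, which receives one arm only.

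Sequence generation {16a} uses the other definition: "Each participating EMS region (Gütersloh, Minden-Luebbecke, and Osnabrueck) will represent a cluster". It adds: "After 6 months, the clusters will switch to the opposite group".

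The analysis section {20a} follows the region definition. For the primary outcome, "a mixed logistic regression model will be used to analyze the difference in the probability of achieving ROSC between the two groups", with the clusters identified in parentheses as the EMS regions. It continues: "Random effects will be included to account for variability between EMS regions". The covariates named are age, comorbidities and other baseline characteristics. Period is not named, and neither is any term for a region within a period.

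On purpose, Trial design {8} calls the trial a pilot "designed primarily to assess the feasibility and preliminary effects of the intervention rather than to definitively establish superiority". Sample size {14} gives about 600 cases, about 300 per group, without a power calculation, and says effect size estimates may inform a later confirmatory trial. Sample size {14} and Additional statistical considerations both state the hypothesis that PEEP "increases the probability of ROSC compared with ZEEP".

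**The concern.** Every region contributes patients to both arms, so PEEP is compared with ZEEP within regions. A region intercept describes how regions differ on average over the year, and that difference largely drops out of the comparison. What remains as error, besides patient-level noise, is how ROSC in a region moves from one six-month period to the next for reasons other than PEEP. The stated model has no place for this and treats patients of one region as equally correlated within and across periods.

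A calendar shift common to all regions is a second source of error. Recruitment runs from 1 June 2025 to 31 May 2026 (Trial status), so two 6-month periods would split the year into June to November and December to May. Three regions cannot be divided equally between two sequences, so a common shift never cancels fully from a contrast that ignores period.

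At stake is the interval around the ROSC effect. It is the trial's main quantitative output, and a later trial may be sized on it. If it is too narrow, the pilot looks more informative than it is.

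**Working it through.** **Inputs.** From the protocol: 3 regions, 2 periods, one crossover per region, about 600 patients, and ROSC of 30% (the upper limit of the usual range quoted in the background). Assumed: regions of equal size, so 600 / 6 = 100 patients per region-period; two-sided 5%; region-period SD of 0 to 0.25 on the logit scale. At ROSC 30%, an SD of 0.10 is about 0.10 × 0.3 × 0.7 = 2 percentage points, and 0.25 is about 5 points. There is no figure in the plan to reproduce, since the 600 has no alpha, power or effect behind it.

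**Step 1: narrowing.** The sampling variance of the log-odds in one region-period is 1 / (100 × 0.3 × 0.7) = 1/21 = 0.0476. The difference between a region's two periods has variance 2 × (0.0476 + SD²). With two regions on one sequence and one on the other, the period-adjusted PEEP effect is half the difference between the two sequence means, so its variance is

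(1/4) × (1/2 + 1) × 2 × (0.0476 + SD²) = 0.0357 + 0.75 × SD².

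A model without a region-period component reports only the first term, an SE of √0.0357 = 0.189. The ratio of true to reported SE is √(1 + 21 × SD²). The false-positive rate is 2 × [1 − Φ(1.96 / ratio)].

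| Region-period SD | Ratio | Type I error, formula | Type I error, simulation |
|---|---|---|---|
| 0 | 1.00 | 5.0% | 5.3% |
| 0.10 | √1.21 = 1.10 | 7.5% | 7.6% |
| 0.15 | √1.47 = 1.21 | 10.6% | 10.3% |
| 0.20 | √1.84 = 1.36 | 14.9% | 14.9% |
| 0.25 | √2.31 = 1.52 | 19.7% | 19.8% |

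The simulations for SD 0.10 to 0.25 used 40,000 trials each with period already adjusted. The reported SE was 0.192 to 0.193 against a true SD of the estimate of 0.213, 0.234, 0.263 and 0.294. The SD = 0 figure comes from a smaller run.

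Without a period term the variance is (2/3) × (0.0476 + SD²), so the ratio is the same. Simulation of that model gave 5.6%, 7.6% and 15.9% at SD 0, 0.10 and 0.20. A random-intercept logistic model (region SD 0.1, 600 runs) gave 3.7% at SD 0 and 15.2% at SD 0.20.

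**Step 2: omitted period shift.** Set the region-period SD to 0 and let all regions shift by b log-odds between periods. The region-only model has SE √(2/3 × 0.0476) = 0.178. Its bias is b/3 with a 2:1 split of sequences and b if all three regions share a sequence. Under independent randomisation the latter has probability 2/8.

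| b | Type I error, 2:1 split | Type I error, same sequence | Weighted 0.75 / 0.25 | Simulation |
|---|---|---|---|---|
| 0.2 | 6.6% | 20.2% | 10.0% | 11% |
| 0.3 | 8.7% | 39.1% | 16.3% | 17% |

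Much of the inflation comes from the same-sequence allocations. There period and treatment are fully confounded and no model can separate them. With a 2:1 split, a fixed period effect removes the bias.

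**Step 3: information on region-period variance.** Six region-period summaries less five parameters (three region, one period, one treatment) leave 6 − 5 = 1 degree of freedom, or 2 without period. Cluster-level t tests held their level in simulation (about 4% to 6% with no common period shift). With 2 df and no period term, the median 95% interval width on the log-odds scale was 1.30 at SD 0 and 1.71 at SD 0.20, against 0.70 for the region-only model.

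**The case against.** The strongest reply is that the size of the problem is assumed. The protocol reports no intracluster correlation or region-period variance, and at SD = 0 coverage is close to nominal. That stands, which is why the figures are a range starting at zero.

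A second reply is that full random-effect structure and small-sample degrees of freedom are usually left to the SAP, which is not shown and could add what is missing. That would be decisive if {20a} were silent. But {20a} states the correlation structure and equates clusters with regions, while Trial design {8} defines them as region-periods. A statistician who follows {20a} as written gets the narrow interval.

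A third reply is that the protocol disclaims definitive superiority and power and sets no significance threshold. That is correct, and it limits the point to the interval and how it is read.

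Three stronger readings are tempting but not supported:

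- A reader might infer that the ROSC hypothesis cannot be tested at all. With eight possible allocations, a randomisation test cannot give a two-sided p below 2/8 = 0.25, but the protocol plans no such test. A t test on region-period summaries is possible, with low power: for 30% vs 40%, about 20% to 30% on 2 df and 10% to 15% on 1 df, at SD 0.20 and 0 respectively.
- A reader might blame the small number of regions itself. Three regions make region-period variance very hard to estimate, but the narrowing comes from leaving that variance out.
- A reader might expect fixed region effects to cure it. Fixed region and period effects without a region-period allowance give the same narrow interval; the 40,000-trial figures above already include period adjustment.

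That recruitment and adherence are promised in Sample size {14} but absent from Outcomes {12} is a separate, minor matter.

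**Conclusion.** The concern holds in this form: the cluster definition is inconsistent, and the primary model as stated leaves region-period variation out of the error and any common period shift in the PEEP contrast. Over assumed region-period SDs of 0 to 0.25, the nominal 5% error becomes about 5% to 20%, and intervals are too narrow by a factor of about 1.0 to 1.5. An unmodelled common shift of 0.2 to 0.3 log-odds gives about 11% to 17%, averaged over independently randomised sequences. These figures assume about 100 patients per region-period and ROSC of 30%. The direction of the error does not depend on those values; the size does. It does not follow that the trial is invalid or that its hypothesis is untestable.

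**What to change.** 1. Use one definition of cluster in Trial design {8}, Sequence generation {16a} and {20a}, and correct the statement about 1:1 allocation within each cluster to match.
2. Add a fixed period effect to the primary model. It can be estimated only if the three regions are not all on the same sequence. If they are, report that period and treatment are confounded.
3. Report the ROSC effect as an estimate whose interval carries region-period variance. Either analyse region-period summaries with t-based degrees of freedom (1 with period in the model), or give a table of intervals over assumed region-period SDs of 0, 0.10, 0.15, 0.20 and 0.25. With the inputs above, the normal-theory 95% half-widths, 1.96 × √(0.0357 + 0.75 × SD²), would be 0.37, 0.41, 0.45, 0.50 and 0.56 log-odds.
4. Do not present the SD = 0 interval or its p-value as the test of the hypothesis in Sample size {14} and Additional statistical considerations.

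The cost is protocol and SAP wording and a small amount of analysis. Trial conduct does not change. Because recruitment has started, the change should be fixed before outcome data are analysed. If it is made as a protocol amendment, {25} requires the ethics committee and centres to be informed, and the centres to receive additional training. The scientific price is a wider, less favourable interval, and on 1 degree of freedom a very wide one, so the table over assumed SDs is likely to be the more useful of the two options.

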### Additional statistical considerations

All analyses will be conducted on an intention-to-treat basis. Exploratory subgroup analyses are planned to evaluate potential effect modifications, including presumed etiology of OHCA (respiratory/asphyxial vs. primary cardiac) and airway management difficulty. These analyses will be hypothesis-generating and interpreted with caution.

The study hypothesis is that ventilation with PEEP (5 mbar) increases the probability of ROSC compared with ZEEP (0 mbar).

No interim analyses are planned.

### Interim analyses {21b}

Interim analyses are not planned during the 1-year study phase.

### Methods for additional analyses (e.g., subgroup analyses) {20b}

Exploratory subgroup analyses are planned to evaluate potential effect modifications related to the study intervention.

The presumed etiology of OHCA — categorized as respiratory/asphyxial versus primary cardiac — will serve as a key subgroup variable. This classification will be based on dispatcher information, scene findings, and the EMS team’s clinical impression.

In addition, the eCRF systematically records a broad range of parameters that allow for further exploratory analyses, including:Patient comorbidities (e.g., cardiac or pulmonary disease)Airway management characteristics (type of device, number of attempts, complications)Ventilation parameters (PEEP, FiO₂, etCO₂, SpO₂, pCO₂)

These variables will enable investigation of potential effect modifiers and interactions, such as which patient groups may particularly benefit from PEEP during resuscitation.

All subgroup analyses will be pre-specified, and interpreted with caution given the pilot nature of the study. The results will be considered hypothesis-generating to guide the design of future confirmatory research.

### Methods in analysis to handle protocol non-adherence and any statistical methods to handle missing data {20c}

Missing or incomplete data will be monitored continuously through automated completeness checks within the eCRF. In cases of protocol non-adherence or deviations in data entry, the coordinating center will contact the respective EMS team for clarification and data verification.

All missing data and deviations from the protocol will be documented and reported transparently.

For the statistical analysis, missing data will be handled using appropriate methods depending on the type and extent of missingness. If feasible, multiple imputation will be applied for missing covariate data. Sensitivity analyses will be conducted to evaluate the robustness of the primary results under different assumptions regarding missingness and protocol adherence.

This approach ensures transparency, minimizes potential bias, and maintains the methodological rigor of the study despite the operational challenges of data collection in the pre-hospital setting.

### Plans to give access to the full protocol, participant-leveldata and statistical code {31c}

Not applicable.

## Oversight and monitoring

### Composition of the coordinating center and trial steering committee {5d}

The coordinating center is comprised of a central team responsible for day-to-day management, operational support, and data coordination. This team ensures that all study procedures are implemented according to the protocol and meets regularly to monitor progress.

In addition, the trial steering committee provides overall oversight, strategic guidance, and ensures adherence to the study protocol. This committee meets at predetermined intervals throughout the trial to review progress and address any issues. Supporting groups, such as the endpoint adjudication committee and the data management team, are also involved in maintaining data quality and trial integrity.

It is important to note that no interim analyses are planned during the course of the trial.

### Composition of the data monitoring committee, its role and reporting structure {21a}

In this trial, a formal Data Monitoring Committee (DMC) has not been established. Given the pilot nature of the study, the limited risk associated with the interventions—which consist of standard resuscitation practices—and the absence of planned interim analyses, a dedicated DMC is not deemed necessary. Instead, oversight of the trial is provided by the coordinating center and the trial steering committee, which meet regularly to monitor safety, data quality, and overall study progress. These groups operate independently from the sponsor and any potential competing interests, ensuring that safety concerns are promptly addressed. Further details regarding trial oversight can be found in the trial’s governance documentation.

### Adverse event reporting and harms {22}

All adverse events (AEs) and unintended effects of the trial interventions will be systematically collected, assessed, reported, and managed. Both solicited events (actively monitored) and spontaneously reported events by the emergency team will be documented using standardized reporting forms within the eCRF. Each event will be evaluated for severity, causality, and expectedness by the designated study team. Serious adverse events (SAEs) will be reported promptly to the trial steering committee and the ethics committee, and managed according to established protocols. Regular reviews of AE data will be conducted to ensure ongoing participant safety and, if necessary, to inform modifications to the trial conduct. Comprehensive details on the adverse event management process are provided in the trial’s standard operating procedures.

### Frequency and plans for auditing trial conduct {23}

N/a.

### Plans for communicating important protocol amendments to relevant parties (e.g., trial participants, ethical committees) {25}

In the event that amendments are necessary, both the ethics committee and the participating centers will be informed. The participating centers will then also receive additional training.

### Dissemination plans {31a}

After the study is completed, a central evaluation of the collected data will be carried out. The participating centers will then receive individualized data for their respective study center. However, the publication of the overall data will be done collectively for all participating sites.

## Discussion

In recent decades, numerous studies have demonstrated the importance of high-quality chest compressions and early defibrillation for the prognosis of patients requiring resuscitation.

While the implementation of optimal initial airway management using ETI or EGA has been the subject of numerous studies and controversial discussions in recent years, there is surprisingly little evidence with regard to the optimal ventilation strategy for patients following airway management. This is all the more astonishing as, due to the continuously decreasing PaO_2_ during circulatory arrest, ventilation obviously becomes more important to ensure tissue oxygenation as the duration of resuscitation increases.

Animal studies have shown that after induction of circulatory arrest, the cessation of spontaneous breathing as well as mechanical chest compressions cause a large part of the lung to exhibit relevant atelectasis (in up to 73% of the lung surface), which could impair gas exchange on the one hand and hemodynamics on the other. Although a favorable effect on prognosis has been demonstrated for the application of a FiO_2_ of 1.0 during resuscitation of adult patients, there is no evidence to date for the oxygenation factor of PEEP, which is particularly important in intensive care medicine. The application of PEEP during resuscitation could improve DO2 and thus the oxygenation of organs at risk, such as the brain, by recruiting and keeping previously atelectatic lung areas open, and could also have a positive effect on hemodynamics.

This study faces several practical and operational challenges related to its conduct in a pre-hospital emergency setting. One key issue is the logistics of enrolling patients during OHCA, where time-sensitive decisions must be made. Ensuring that EMS personnel adhere to the study protocol while delivering urgent care will require thorough training and clear communication. Another challenge is the cluster-randomized design, which involves different EMS regions rotating between the PEEP and ZEEP groups. This design requires careful coordination and monitoring to ensure that randomization is properly implemented and that no unintentional crossover occurs between groups. To ensure this, it is planned to program the emergency ventilation modes of the ventilators according to cluster randomization. In addition, regular training sessions and stickers placed on the ventilators are intended to make rescue service staff aware of which group the patient is in at the time of resuscitation.

Additionally, data collection during such high-pressure, fast-paced environments may be difficult. Ensuring accurate and complete documentation of ventilation settings and patient outcomes will be critical. For this reason, it is planned to document the measures taken following the operation using an application-based eCRF. In addition, the emergency respirators will be read out after use so that real-life data on the ventilation settings measured by the respirators is available.

Moreover, variability in care practices across EMS regions may introduce confounding factors that will need to be accounted for in the statistical analysis.

However, the treatment of resuscitation is highly standardized by the regularly updated resuscitation guidelines and the rescue service staff in Germany are regularly re-certified in the performance of CPR in accordance with their legally prescribed further training obligation.

These issues, along with the ethical considerations of conducting research in life-threatening situations, will need careful attention throughout the study.

## Trial status

This is the second version of the protocol. Recruitment commenced on June 1, 2025, and is expected to be completed by May 31, 2026. The study is currently ongoing across the participating emergency medical service (EMS) regions.

## Data Availability

The principal investigator will have access to the anonymized final trial dataset. The other study coordinators have access to the data records in their respective study centers.

